### Data Collection

#### NoMAD Instrument

Participants will complete 2 data collection forms at the beginning, and forms will also be completed after the ELNEC-PPC training. The main data collection instrument is NoMAD [33]. The original form of this instrument has been translated into Arabic and adapted to Arabic conditions to evaluate the normalization potentiality of PPC training, which will be provided by a web-based training intervention.

The NoMAD instrument has been translated into the Fusha dialect in translation steps outlined previously [60]. The authors translated the NoMAD instrument from English to Arabic, and then, back translated it to English. The content validity and translated NoMAD acceptability have been measured in a reiterative procedure involving several recognized steps, including translation forward and translation backward, tests of the target language instrument content validity, meetings with specialists, and further revision, as well as a final content validity test of the studied tool. The finalized tool has been created as an electronic form. The Arabic NoMAD prime version, following step 2 of the clarification and adaptation process, has been applied in a pilot study. The Arabic NoMAD instrument is split into the following 3 sections: Section A, which includes 12 items on the respondents; Section B, which includes 3 general items on the intervention; and Section C, which includes 20 identifiable items on the intervention. Regarding the 4 NPT concepts, “Coherence” has 4 questions, “Cognitive Participation” has 4 questions, “Collective Action” has 7 questions, and “Reflexive Monitoring” has 5 questions.

The Arabic NoMAD scale consists of 31 Likert-type items. The items in section B are rated on a 10-point Likert-type scale from “not at all” to “completely.” The items in section C are rated on a 5-point Likert-type scale from “disagree strongly” to “agree strongly.” “Neutral” and “not applicable” are also assumed as choices to explain respondents’ experiences of using the intervention within the workplace (Multimedia Appendix 9). A total of 30 participants have completed the Arabic NoMAD survey, with a 100% reply rate. Content validity computed for the Arabic NoMAD scale (content validity index [CVI]) was 0.91, which is significantly higher than the suggested level of 0.80, and the item-CVI was 0.71-1.00. Scale reliability was also strong, with a Cronbach α coefficient of .77-.86 in the postcourse analysis. In a recent study, the NoMAD instrument demonstrated an indoor consistency score (α coefficient) of .76-.83 [61], and therefore, it may be considered as reliable.

The NoMAD questionnaire has been translated into 7 languages [62]. The Arabic NoMAD instrument provides a versatile “bank of items” [63], with a focus on wide item versions, for instance, to supply more anticipatory assessments. The NoMAD designers propose that the tool must be examined as a “pragmatic measure” of an intervention [64,65], and it motivates adaptation for multipurpose functions in particular application studies and meets clinical practice requirements.

The Arabic NoMAD instrument has 4 building item groups, according to reliability and validity data. In addition, there is no proposal for definite scoring instructions or construct procedures, which should be used in each study.

The time to complete the baseline questionnaire is approximately 20-25 minutes. The follow-up questionnaires are shorter, and the time to complete these is approximately 20 minutes.

At the starting point and 2-week and 3-month follow-ups, participants will be sent an email with a link that directs them to complete the Arabic NoMAD questionnaire. To ensure as high a response rate as possible in the follow-up questionnaires, several reminder emails will be sent (every 3 days). If no response is received, the investigator will attempt to communicate with the participant via text message or phone call and inquire if the participant is ready to reply to the survey over the telephone.

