Each participant in the intervention group will complete all 9 modules of the ELNEC-PPC training course. Meanwhile, the main investigator will follow-up with the participants entering the website link and ask them via an instant message or email about the completion of steps and upload of a screenshot for each module to a Google Form URL provide to them.

After 2 weeks, the main investigator will make sure that all participants in the intervention group have completed the tasks assigned to them during the course, by asking the participants via an instant message or email, and will also send certificates for each module. Then, the electronic questionnaire (Arabic NoMAD) will be sent again to be filled out for the second time by the intervention group, and the main investigator will make sure that all the forms have been completed within 2 weeks after the training course. After that, the participants will be monitored at their workplaces for 3 months in order to measure the impact of the training course on their work and the changes that affect their roles, as well as evaluate their experiences using the NPT toolkit. Interviews will be conducted at their workplaces in the selected hospitals.

After 3 months, the main investigator will measure the variables of the interview using the NPT toolkit to create a viewpoint for PPC delivery via nurses at the end of life, and assess the modality of working in the hospital units. Simultaneously, a NoMAD link will be sent to all participants from the 2 arms for the last time to evaluate the long-term impact of the training course on providing PC.

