#### Primary Outcome

The primary outcome involves the evaluation of the ELNEC-PPC course aimed at providing PC in a range of health care contexts through the Arabic NoMAD questionnaire and observation of routine clinical care.

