### Statistical Analysis

Results will be stated according to the CONSORT declaration concerning health [49,50]. The analysis of primary data will follow the intention-to-treat principle and relate the alterations in the overhead outcome measures between the intervention and control groups. SPSS Version 26.0 software (IBM Corp) will be used for the data analysis. Descriptive statistics will be presented by percentage distributions and indicators describing the location (arithmetic mean=M) and deviation (range; standard deviation=SD). The analysis of primary data will predict the mean difference with 95% CI in the NoMAD score at the 3-month follow-up between the intervention and control groups.

The model includes accessible data of nurse participants at all time points (ie, starting point, and after 2 weeks and 3 months). Within the regression model, distinct participants will be considered using a random effect approach, accounting for inside topic covariance construction. The group and time effects will be considered with asset effects using a combined intervention and time variable. Starting point levels will be obtained over 2 research collections supposing that starting point alterations are coincidental [66]. This is aimed at minimal starting point changes in the outcome variable.

Both groups will primarily be labeled according to their starting point features. The initial data will be analyzed to evaluate the effectiveness of ELNEC-PPC web-based training in the intervention group when compared with the findings in the control group, according to the NPT.

The analysis will inspect intervention effects continuously over time, and will assess the interaction between period and group allocation. The difference between the groups will be assessed for the period of the basic model and will be further evaluated according to the stratification by unit category (critical care unit and noncritical care unit) [67].

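### The primary NoMAD contrast asks both arms about an intervention only one arm has used by 3 months, so it can partly reflect having taken the course

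*Protocol article*

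**What the plan says.** Statistical Analysis sets the primary result as the "mean difference with 95% CI in the NoMAD score at the 3-month follow-up between the intervention and control groups". Process of Implementation confirms that at 3 months "a NoMAD link will be sent to all participants from the 2 arms for the last time". Under Primary Outcome, "The primary outcome involves the evaluation of the ELNEC-PPC course aimed at providing PC in a range of health care contexts", measured with the Arabic NoMAD and by observation of routine care.

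The NoMAD Instrument section says the tool was adapted to judge how far the web-based training could become normal practice. It lists 12 items about the respondent (section A), 3 general items on the intervention rated on a 10-point scale (section B), and "Section C, which includes 20 identifiable items on the intervention", rated on a 5-point scale and split into four constructs of 4, 4, 7 and 5 items. Neutral and not-applicable options are offered so that respondents can describe their "experiences of using the intervention within the workplace". The same section states that "The Arabic NoMAD scale consists of 31 Likert-type items" and that "there is no proposal for definite scoring instructions or construct procedures".

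Usual Care gives control nurses access to a similar course only after the trial is complete.

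**The concern.** A between-arm contrast needs an outcome that means the same thing in both arms. Here the items are described by reference to the intervention and to experience of using it. At the primary time point the control arm has no such experience, and at baseline neither arm has. A control nurse could reasonably answer not applicable, answer neutral, or disagree because there is nothing to agree with. Any of these can separate the arms even if palliative care in the units is no more embedded in one arm than in the other.

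The trial would then risk reporting as normalization what is partly a record of course attendance. The Discussion says the results will help policy makers decide whether to extend the program to all nursing staff in the country, so the distinction matters. The limitations listed there cover lack of blinding and self-report but not this point.

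**Working it through.** **1. What the items refer to, and who can answer.**
- Contrast: NoMAD at 3 months, intervention versus control (Statistical Analysis). Both arms complete it (Process of Implementation).
- Referent: sections B and C are items on the intervention, and the tool evaluates the ELNEC-PPC course or training (NoMAD Instrument, Primary Outcome).
- Control exposure up to 3 months: none (Usual Care).
- Control-arm wording: none described. The nearest text says the item bank can serve more anticipatory assessments, without specifying such a version.
- Reliability: the reported alpha of .77-.86 comes from the post-course analysis, and every pilot participant received the intervention (Pilot Testing). The article reports no alpha for untrained respondents.

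**2. How large an artefact could be.** The article gives no not-applicable rate and no coding rule, so these inputs are assumptions: no true effect, 86 nurses per arm, 20 items scored 1-5, item mean 3.5, SD between nurses 0.6, SD within nurse 0.8, and not applicable chosen at random at rate q by control nurses only. There were 600 simulated trials per setting.

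Approximate shift of the control mean:
- coded 0: 3.5 × q
- coded neutral (3): (3.5 − 3) × q = 0.5 × q
- answered items averaged: 0

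| q in controls | Shift, coded 0 | Simulated d | Shift, coded neutral | Simulated d | Share of trials with P<.05, neutral |
|---|---|---|---|---|---|
| 10% | 0.35 | 0.60 | 0.05 | 0.09 | 10% |
| 20% | 0.70 | 1.19 | 0.10 | 0.19 | 22% |
| 40% | 1.40 | 2.46 | 0.20 | 0.40 | 73% |

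Rough check: 0.35 / 0.6 ≈ 0.58, close to the simulated 0.60. Coding as 0 gave P<.05 in 97% to 100% of trials. Averaging answered items gave d about 0 and P<.05 in 4% to 6%.

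**3. Scale.** The Sample Size section states no effect size. Its 86 per arm is reproduced if d = 0.5 is assumed: two-sided alpha 0.05 and power 0.90 give 85.03 by the t test, rounded up to 86, and power at 86 is 0.903. If that was the target, neutral coding at 40% would produce most of it spuriously (0.40), and coding as 0 at 10% would exceed it (0.60).

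**4. What the simulation leaves out.** It covers only the not-applicable route. Control nurses who give a rating, but of a course they have not used, add a difference of meaning that no coding rule removes. Averaging answered items is also unbiased only when not applicable is unrelated to the answer. If control nurses choose it where they would otherwise disagree, the control mean is too high and the difference too small.

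**5. Item count, a separate matter.** A = 12, B = 3, C = 20. The sums are A+B = 15, A+C = 32, B+C = 23 and A+B+C = 35. None is 31. The construct counts do agree with section C: 4 + 4 + 7 + 5 = 20.

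**The case against.** The strongest reply is that the actual item wording is in Multimedia Appendix 9, which is not shown. The article uses the word intervention loosely: Trial Design describes the tested condition as providing pediatric palliative care with usual care, and the arm carries that name. Control nurses could answer items about providing such care. This is possible and is why the fix allows for confirmation from the appendix. It runs against Primary Outcome and NoMAD Instrument, however, which tie the tool to the course or training and to experience of using it.

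A second reply is that scoring and the handling of not applicable belong in an analysis plan, and that the remark about scoring instructions may mean only that NoMAD prescribes no universal rule. That is fair, and a missing scoring rule alone would be no finding. But a scoring rule cannot change what the items mean to nurses without the course.

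A third reply concerns size, and it stands. A reader might infer a false difference of 0.70 points, for example 0.9 × 3.5 = 3.15 against 0.7 × 3.5 = 2.45 with not-applicable rates of 10% and 30%. That needs assumed rates and coding as 0, a rule the article nowhere adopts. Nor does the article show that control nurses will choose not applicable often.

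**Conclusion.** The concern holds in this form: as described, the primary contrast can partly measure course exposure, because the items refer to an intervention that one arm has not used by 3 months and nobody has used at baseline. The size of any artefact is unknown. Under the stated assumptions it runs from about 0 (answered items averaged, not applicable unrelated to the answer) through 0.09-0.40 (coded neutral) to about 0.6-2.5 (coded 0).

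Three stronger inferences are not supported:
- **Multiplicity.** Four constructs each tested at .05 would give 1 − 0.95^4 = 18.5% familywise error if independent, but Statistical Analysis names one score at one time point and does not make four construct tests primary.
- **Item count as a source of bias.** The figure of 31 is a reporting inconsistency. It leaves the scale's composition unclear but creates no difference between arms.
- **23 as the correct count.** B+C = 23 follows from the sections whose rating scales are described, but the article does not say whether any section A item is Likert-type. Only reconciliation against Multimedia Appendix 9 is justified.

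**What to change.** - **Items.** In both arms and at all time points, make the items refer to providing pediatric palliative care in the nurse's unit, or confirm that Multimedia Appendix 9 already does. If data are already collected (the Results section expected completion by March 2021), state instead that the contrast cannot separate course exposure from normalization.
- **Score.** Before unblinding, define the NoMAD component of the primary outcome as the mean of the answered section C items (1-5). Never score not applicable as a value. Report its rate by arm, with a sensitivity analysis in which it is informative.
- **Secondary.** Report the 10-point section B and the four constructs as secondary. The observation component named under Primary Outcome is not altered by this change.
- **Count.** Reconcile 31 with the section counts (B+C = 23, A+B+C = 35) against Multimedia Appendix 9.

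Cost: the scoring and reporting changes need about a paragraph of text. Rewording departs slightly from the piloted form, so the reported content validity index (0.91) and alpha would carry over only approximately. It is useful only if applied from baseline on, since a change midway would make baseline and follow-up items differ.

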#### Interviews

Semistructured face-to-face interviews will be conducted with all nurse participants to detect the level of successfully passing the ELNEC-PPC web-based training course from the selected settings. All participants have direct contact with patients, and 3 rounds of interviews will be conducted after 3 months. After consenting, participants will be interviewed by the main researcher (MA). All interviews will be audio recorded and transcribed. If participants do not want to be recorded, the researcher will take notes and subsequently write a detailed account of the discussion. Some participants will be interviewed in pairs or small groups. They will be asked about the changes they experienced with regard to training.

The interactive NPT toolkit will be used for assessment. It contains 16 questions for thinking through an implementation problem. The embedding will be improved, and statements and explanations will be edited for a web-enabled tool.

### Access to Data

All personally identifiable data collected in the trial will be kept for 5 years. These data are kept to be able to track any adverse events reported after completion of the trial. After these 5 years, the data set will be fully anonymized. The anonymized full data set will be kept for up to 30 years for research purposes and will be used to create a data model that can inform the further development of potential research of ELNEC-PPC web-based training. Data will be stored at the Postgraduate Department of Nursing College/Babylon University.

### Statistical Analysis

Results will be stated according to the CONSORT declaration concerning health [49,50]. The analysis of primary data will follow the intention-to-treat principle and relate the alterations in the overhead outcome measures between the intervention and control groups. SPSS Version 26.0 software (IBM Corp) will be used for the data analysis. Descriptive statistics will be presented by percentage distributions and indicators describing the location (arithmetic mean=M) and deviation (range; standard deviation=SD). The analysis of primary data will predict the mean difference with 95% CI in the NoMAD score at the 3-month follow-up between the intervention and control groups.

The model includes accessible data of nurse participants at all time points (ie, starting point, and after 2 weeks and 3 months). Within the regression model, distinct participants will be considered using a random effect approach, accounting for inside topic covariance construction. The group and time effects will be considered with asset effects using a combined intervention and time variable. Starting point levels will be obtained over 2 research collections supposing that starting point alterations are coincidental [66]. This is aimed at minimal starting point changes in the outcome variable.

Both groups will primarily be labeled according to their starting point features. The initial data will be analyzed to evaluate the effectiveness of ELNEC-PPC web-based training in the intervention group when compared with the findings in the control group, according to the NPT.

The analysis will inspect intervention effects continuously over time, and will assess the interaction between period and group allocation. The difference between the groups will be assessed for the period of the basic model and will be further evaluated according to the stratification by unit category (critical care unit and noncritical care unit) [67].

Repeated measures ANOVA will be performed to assess the multivariate main intervention effects (associated with controls) considering pre, post, and follow-up time points, as well as their interface effects. A 2-sided *P* value <.05 will be considered significant. The standardized effect size (Cohen *d*) will also be calculated. Mediator analysis will be controlled to determine which subgroups would benefit further from the intervention, with outcome variables regressing on independent variables, including age group, sex, education, and starting Arabic NoMAD score.

Secondary outcomes will be analyzed using an approach similar to the approach described for the primary outcome with linear mixed models for repeated measures. The data from the 2-week and 3-month follow-ups will also be analyzed using the approach described above for the primary outcome.

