### Randomization

Participants will be randomized to either (1) ELNEC-PPC web-based training as well as usual care or (2) only usual care. The randomization involves block randomization plus permuted blocks of random size known to the researcher and stratified by the type of unit (ie, critical care unit and noncritical care unit). The allocation ratio between the intervention and control groups is 1:1. Randomization will be performed using the Sealed Envelope website [53].

Randomization involves generating random numbers using a computer. The numbers are distributed and written on the nomination forms for the training course in the text boxes on the top of the forms. According to the sample size, the first random number represents the intervention group and will be written on the form with the code “T,” and the random number for the control group will be written with the code “C.” The forms are placed in sealed envelopes, and these are mixed and placed in a large sealed envelope (A3) (Multimedia Appendix 8). These steps represent the randomization process performed by a nurse. A video is made of the process of preparing the sealed envelopes, with the participant details visible. A second researcher will later view the video to ensure the accuracy of the process. Corresponding envelopes will be opened only by the participants who select them, and they will be allocated accordingly. The enrolled participants will complete all baseline assessments.

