### Sample Size

The study has been designed as a superiority trial with 2 parallel groups (ELNEC-PPC web-based training plus usual care and usual care only). For calculation of the appropriate sample size, the main researcher uses the assumption that the 5 selected settings have 254 nursing staff members on average eligible for inclusion based on a survey of all included settings before the study to determine the total number of nurses who work in the selected settings and are appropriate for inclusion. Based on this assumption, as well as a 2-sided *P* value <.05, a 0.90 power, a traditional predictable correlation between 2 measurements of 0.5, and an intraclass correlation coefficient with *P*<.05, 86 participants were required in the intervention group and 86 were required in the control group for *t* tests. To support equal sample sizes, including for the units of the selected settings, and to account for intrastratified correlations of units, a multilevel analysis will be used. Nursing staff members who are transferred to a dissimilar organization unit will be exchanged from the sample of nursing staff, and changes will take place in the course of the study. To catch up with nursing staff members who are not changed in time, the researchers will insert an additional organization unit from the critical care units for the intervention and control groups, which will result in a total of 172 nursing staff members. All power analyses will be performed using the G*Power software (version 3.1).

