**Figure 2 figure2:**
[figure not shown]
Illustration of the End-of-Life Nursing Education Consortium-pediatric palliative care web-based training intervention trial according to the Pragmatic Explanatory Continuum Indicator Summary-2 wheel.

The trial has some limitations that must be mentioned. First, the participants will be aware of the intervention being received, which might cause bias. Second, as self-reported data will primarily be used, there might be recall bias. Third, a high dropout rate is likely, even with self-choice and additional strategies to reduce it (for instance, email notices in addition to further incentives). Fourth, the outcomes will be assessed up to only 3 months. Finally, the self-administered web-based intervention might be less efficient.

Up to now, the readiness of nursing staff to join the ELNEC-PPC web-based training course has been outstanding. The first training was provided in March 2020 for the pilot study, and the last training was provided in August 2020. The results became accessible in December 2020. The study will involve numerous departments. All units have a bottom-up approach for offering PC to children with life-limiting illnesses.

The selected design is appropriate for the study purposes. The design permits evaluating the training program’s influences on normalization and adaptation for providing PPC during daily routine practice promptly. In addition, a brief assessment will be performed at 3 months.

We hope that the findings of this study show that the web-based training intervention not only supports nursing staff in providing PPC in addition to usual care, but also has a positive impact on high-quality nursing care in pediatric governmental health care organizations and provides knowledge about recovery in children with life-limiting illnesses. Health care workers will be able to provide original information intended for modifying the intervention according to their patients’ needs. The results will help health care policy makers decide whether to expand the ELNEC-PPC program to all nursing staff in the country.

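### An unranked repeated measures ANOVA sits beside the intention-to-treat mixed model; it uses completers only in its standard form, and its group effect is not the 3-month difference

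*Protocol article*

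**What the plan says.** The protocol article, Statistical Analysis, describes two analyses of the training effect on NoMAD.

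- **Mixed model.** "The analysis of primary data will follow the intention-to-treat principle", and the quantity to be estimated is the between-arm mean difference at 3 months with its 95% CI. "The model includes accessible data of nurse participants at all time points", with a random effect for each nurse. The baseline level is pooled over the arms because baseline differences are taken to be chance.
- **ANOVA.** "Repeated measures ANOVA will be performed to assess the multivariate main intervention effects (associated with controls) considering pre, post, and follow-up time points". The sentence goes on to include interaction effects. The next sentence is: "A 2-sided *P* value <.05 will be considered significant". Nothing says whether this analysis is primary, supportive or a sensitivity analysis.

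Later in the same section, secondary outcomes are to follow the primary-outcome approach, which is there called linear mixed models for repeated measures.

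Sample Size specifies "a 0.90 power, a traditional predictable correlation between 2 measurements of 0.5" and concludes that "86 participants were required in the intervention group and 86 were required in the control group for *t* tests". It states no effect size. Among the limitations in the Discussion: "a high dropout rate is likely, even with self-choice and additional strategies to reduce it".

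**The concern.** The two analyses address the same intervention effect but differ in whom they include and in what they estimate.

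- **Who is included.** The mixed model uses every nurse who supplied any score. Repeated measures ANOVA, as normally run in SPSS (the software the article names), needs all three scores and drops a nurse who misses one.
- **What is estimated.** The mixed model targets the 3-month difference with a common baseline. The ANOVA group effect is the average difference over three visits, one of which precedes training. The ANOVA interaction is a two-degree-of-freedom test of any difference in profile. Neither is the 3-month difference.

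Both can be read at P<.05 with no stated order. If they disagree, the article gives no explicit rule for which one answers the trial's question.

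**Working it through.** **Inputs.** Two-sided alpha 0.05 (Statistical Analysis). Power 0.90, correlation 0.5, 86 per arm, t tests (Sample Size). "The allocation ratio between the intervention and control groups is 1:1" (Randomization). Three visits: baseline, 2 weeks, 3 months (Outcomes). *Assumptions:* effect size in SD units, equal variances and correlations at all visits, no clustering. No dropout rate is given, so a range of 5% to 30% is shown.

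**Step 1: the plan's own figure.** Because no effect size is stated, 86 per arm cannot be reproduced from the stated inputs alone. With d = 0.5, the noncentrality is 0.5 × √(86/2) = 3.28 on 170 df and power is 0.903. 86 is the smallest n per arm that reaches 0.90. Solving for exactly 0.90 gives d = 0.497. A change score at correlation 0.5 has SD √(2 × (1 − 0.5)) = 1 and so needs the same n. I therefore take d = 0.5 as an assumption.

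**Step 2: what the ANOVA group effect estimates.** With differences 0, δ₂ and δ₃ at the three visits, it estimates (0 + δ₂ + δ₃)/3. If δ₂ = δ₃ = δ, that is 2δ/3. A chance baseline difference enters with weight 1/3. The variance of a nurse's three-visit mean is (1 + 2ρ)/3, which is 2/3 at ρ = 0.5 (SD 0.816). This step does not depend on the effect size or on dropout.

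**Step 3: illustrative power, 86 per arm, complete data, δ₂ = δ₃ = 0.5, ρ = 0.5.**

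- ANOVA group effect: 0.333/0.816 = 0.408 SD, power 75.9%. For 90% it would need 128 per arm.
- ANOVA group-by-time interaction: noncentrality (86/2) × (0.25/0.75) = 14.33 on 2 df, power 92.9%.
- Baseline-adjusted 3-month contrast, approximating the mixed model: 0.5/√(1 − 0.25) = 0.577 SD, power 96.4%.

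**Step 4: sensitivity of the ANOVA group effect.**

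- δ₃ held at 0.5, ρ = 0.5: with δ₂ = 0.25 the shift is 0.25 and power 51.5%; with δ₂ = 0.75 the shift is 0.417 and power 91.4%.
- δ₂ = δ₃ = 0.5: ρ = 0.3 gives 84.5%, ρ = 0.7 gives 68.1%.

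**Step 5: completers only** (δ₂ = δ₃ = 0.5, ρ = 0.5).

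| Incomplete | Complete per arm | Power, ANOVA group effect |
|---|---|---|
| 5% | 82 | 73.8% |
| 10% | 77 | 71.1% |
| 20% | 69 | 66.3% |
| 30% | 60 | 60.2% |

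With 69 per arm the interaction has 86.1% and the baseline-adjusted 3-month contrast 92.0%. The fall from 96% to 76% in Step 3 comes from which contrast is tested, not from dropping nurses. Step 5 adds the loss from dropping them.

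**The case against.** The strongest reply is that the primary analysis is already identifiable. The intention-to-treat statement and the 3-month difference are tied to the mixed model, and the later wording on secondary outcomes calls the primary approach linear mixed models. On the illustrative figures that model has about 96% power. This largely stands: the mixed model is probably meant as primary. But it has to be inferred, and the ANOVA keeps its own significance threshold.

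Second, the ANOVA sentence also plans the interaction, which has about 93% power on the same assumptions. Its reference to multivariate effects may mean the within-nurse tests and not the three-visit average. This stands as a caution about the 76%. It does not make the interaction a test of the 3-month difference.

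Third, the article does not state that incomplete records are deleted. True: that is how the standard procedure works, and a full protocol or SAP might say more. The article nevertheless names this method beside an available-data model and expects high dropout.

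A reader might also infer three stronger claims that the document does not support.

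- *The plan promises 90% power and delivers 76%.* The 90% is stated for t tests, the effect size is not given, and the 76% moves between about 51% and 91% with the assumed 2-week effect.
- *The interaction could wrongly flag an effect that has gone by 3 months.* A fading effect is a true group-by-time difference. The mixed model also plans a group-by-time test, so the same result could arise there.
- *Completers' results would be biased by a known amount.* Any such figure needs an assumed dropout mechanism. The available-data model is itself protected only if dropout depends on observed scores.

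**Conclusion.** The point holds as a conflict between two specified analyses. The mixed model follows intention to treat, uses all available data and targets the 3-month difference. The ANOVA, in its standard form, uses completers only, and its group effect estimates about two thirds of a constant post-training effect with chance baseline imbalance left in. The two-thirds result is structural. The power figures are illustrations under an assumed 0.5 SD effect at both follow-ups and correlation 0.5.

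The primary comparison is not shown to be underpowered, and no contradiction with the stated 90% is established. The practical harm is limited to an unranked second test that can disagree with the primary one. It is worth correcting because the correction costs almost nothing.

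**What to change.** In Statistical Analysis:

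1. State that the between-arm NoMAD difference at 3 months from the mixed model is the single primary test.
2. Take the 2-week difference and the group-by-time test from the same model and report them as supportive.
3. Delete the repeated measures ANOVA, or label it a completers' sensitivity analysis that carries no significance claim.

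The cost is a sentence or two of wording. No new data are needed and the sample size is unchanged. If the ANOVA is deleted, there is one analysis fewer to run.
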